**Table S1 - Organ failure descriptors**

| **Upper airway** positive for inclusion and allocation to primary or secondary organ failure by critical care specialists:   - Stridor - Altered voice - Tongue/oropharyngeal swelling - Obvious laryngeal swelling at 1^st^ laryngoscopy - Gross macroscopic laryngeal swelling at autopsy - Recorded as Negative/No Upper airway involvement if only microscopic/minor laryngeal swelling at autopsy.   Notes: Criteria developed on expert consensus with consideration of upper respiratory descriptors in published grading systems. Laryngeal swelling may occur after multiple laryngoscopy attempts^1^ – first laryngoscopy and autopsy findings have been qualified to take this confounding element into consideration. Number of laryngoscopy attempts is recorded during data extraction. |
| --- |
| **Bronchospasm** positive for inclusion and allocation to primary or secondary organ failure by critical care specialists:   - Persistent cough - Wheeze - Chest tightness with history of asthma - Shortness of breath with history of asthma - Cyanosis or hypoxia <93% with history of asthma (excluding isolated airway obstruction) - Cyanosis hypoxia <93% without documented or clinical hypotension - Increased work of breathing (excluding isolated upper airway obstruction) - Patient’s usual asthma symptoms - Bronchodilator use during episode - High peak inspiratory pressure in intubated patient (subjective or greater than 30cm H2O) - Difficult to ventilate - Upsloping CO2 trace or obstructive airway pattern   Notes: Criteria developed on expert consensus with consideration of lower respiratory descriptors in published grading systems. Airway obstruction, bronchospasm and cardiovascular symptoms can overlap. Criteria have been developed to exclude overwhelming upper airway obstruction in the absence of obvious bronchospasm. Chest tightness and shortness of breath may be a manifestation of cardiovascular involvement if not associated with asthma symptoms or pre-existing asthma increasing the pre-assessment probability of symptom origin. Dyspnoea, cyanosis and hypoxia can overlap with cardiovascular compromise.^2, 3^ Brown reported 12 % of hypotensive patients developed *dyspnoea* where 100% of hypoxic patients had either dyspnoea or wheeze. In the same study 10% of wheezy patients had hypotension. |

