Instructions for allocation of organ failure were derived from agreement of the expert panel of authors incorporating the specialties of Anaesthesia, Emergency Medicine, Allergy and Clinical Immunology, and Primary Care. The panel used a three step process to develop descriptors of organ involvement. The first was mapping descriptors from nine grading systems identifying symptoms of anaphylaxis and two organ specific (asthma and laryngotracheobronchitis severity descriptors) to categorise them as signifying upper airway, lower airway (bronchospasm) and cardiovascular compromise. The second step involved refining criteria with regard to potential overlap of symptoms/signs including consideration of published data as described above in the background section on organ failure interrelation and overlap of symptoms. The third step was revision from individual domains of expertise from each specialty.

The nine acute allergy grading systems and two organ specific severity guides that covered both adult and paediatric anaphylaxis were mapped to extract symptoms of upper airway, lower respiratory obstruction and cardiovascular symptoms to be identified in the immediate lead up to cardiorespiratory arrest in each case.

- One international allergist based system^19^
- One Delphi study designed for all setting and triggers^7^
- One retrospective ED observation study 30% insects, 22% drugs, 18% food^3^
- One published proposal for universal grading (expert opinion)^20^
- Two grading systems designed for drugs^9, 21^
- Three grading systems designed for allergist food trials^22-24^
- One grading system for insect anaphylaxis^25^
- Two clinical practice guidelines for other conditions with single organ involvement^26, 27^

Once organ involvement was deemed to present the data extractors were required to use clinical assessment as to which organ failure contributed to deterioration prior to cardiac arrest.

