**ORGAN FAILIRE TYPES**

- 1. **Upper Airway Oedema present**

| **Definition** | Upper Airway Oedema present during the anaphylaxis episode | | |
| --- | --- | --- | --- |
| **Data name** | Airway Oedema | **Collection** | Manual extraction |
| **Data Type** | Single answer | **Date Started** | 01/05/2024 |
| **Field Size** | Drop down yes/no/not recorded | **Layout** |  |
| **Code Set** | [airway_oedema] = '1' |  |  |
| **Reporting guide** | Yes if ANY of the following present   - Stridor - Altered voice - Tongue/oropharyngeal swelling - Obvious laryngeal swelling at 1^st^ laryngoscopy - Gross macroscopic laryngeal swelling at autopsy | | |
| **Purpose and basis for reporting guide** | To objectively determine presence of upper airway oedema during the anaphylactic reaction that contributed to death.  Criteria developed on expert consensus with consideration of upper respiratory descriptors in published grading systems^3, 7, 21, 30^. Laryngeal swelling may occur after multiple laryngoscopy attempts^1^ – first laryngoscopy and autopsy findings have been qualified to take this confounding element into consideration. Number of laryngoscopy attempts is recorded during data extraction. | | |
| **Outcome #** | **Outcome Text Label** | **Outcome Code Set** | **Definition Note** |
| 1 | Yes |  |  |
| 2 | No |  |  |
| 3 | Not recorded |  | Presence **OR** Absence of symptoms **not** recorded |

- 1. **Bronchospasm present**

| **Definition** | Bronchospasm present during anaphylaxis episode | | |
| --- | --- | --- | --- |
| **Data name** |  | **Collection** | Manual extraction |
| **Data Type** |  | **Date Started** | 01/05/2024 |
| **Field Size** | Drop down yes/no/not recorded | **Layout** |  |
| **Code Set** | [bronchospasm] = 1 |  |  |
| **Reporting guide** | Yes if ANY of the following present   - Persistent cough - Wheeze - Chest tightness with history of asthma - Dyspnoea with history of asthma - Cyanosis or hypoxia <93% with history of asthma (excluding isolated upper airway obstruction) - Cyanosis hypoxia <93% without documented or clinical hypotension - Increased work of breathing (excluding isolated upper airway obstruction) - Patient’s usual asthma symptoms - Bronchodilator use during episode - High peak inspiratory pressure in intubated patient (subjective or greater than 30cm H2O) - Difficult to ventilate - Upsloping CO2 trace or obstructive airway pattern | | |

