## Secondary Objectives

To compare the following outcomes by patient allergen exposure:

1. Time to symptoms from allergen exposure.
2. Time from symptom onset to severe symptoms.
3. Time from severe symptoms to cardiorespiratory arrest.
4. Time from arrest to death.
5. Whether the patient required tracheal intubation.
   1. If required tracheal intubation, the timing of tracheal intubation.
   2. Time to tracheal intubation from cardiorespiratory arrest.
6. Whether the patient experienced vomiting or aspiration.
7. Whether the patient received cardioversion (defined as no shocks vs at least one shock).
8. Change in posture.
9. Frequency of deaths per year over time (by allergen exposure and by age group).

To compare primary organ failure by the following complications:

1. Difficult airway (FONA, failed intubation, or 3 or more attempts at intubation)
2. FONA (front of neck access)
3. Vomiting or aspiration
4. Pneumothorax (dichotomised to none OR one+/- both sides)
5. Cardioversion

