**Association of complications with primary outcome and allergen trigger category**

As a condition of ethics approval, death counts of less than five cannot be directly reported. Where this has occurred in tabular reporting, we have abbreviated this to Not Reportable (NR).

**Table S3:** Association between complication and primary organ failure

|  | **Number (%) with specified primary organ failure** | **Number (%) without specified primary organ failure** | **Complete case analysis** | | **Multiple imputation** | |
| --- | --- | --- | --- | --- | --- | --- |
|  |  |  | **Odds ratio (95% CI)** | **p-value** | **Odds ratio (95% CI)** | **p-value** |
| **Primary Organ Failure: Bronchospasm** | | | | | | |
| **Difficult airway** | 21/29 (72.4%) | 101/160 (63.1%) | 1.533 (0.639 to 3.680) | 0.338 | 1.523 (0.668 to 3.473) | 0.316 |
| **Cricothyroidotomy** | 5/13 (38.5%) | 122/193 (63.2%) | 0.364 (0.115 to 1.155) | 0.086 | 0.380 (0.130 to 1.117) | 0.078 |
| **Vomiting or aspiration** | 37/53 (69.8%) | 116/197 (58.9%) | 1.615 (0.842 to 3.098) | 0.149 | 1.774 (0.944 to 3.334) | 0.075 |
| **Pneumothorax** | 11/18 (61.1%) | 129/209 (61.7%) | 0.975 (0.363 to 2.617) | 0.959 | 1.014 (0.363 to 2.835) | 0.979 |
| **Cardioversion** | 26/41 (63.4%) | 32/46 (69.6%) | 0.758 (0.310 to 1.853) | 0.544 | N/A | N/A |
| **Primary Organ Failure: Cardiovascular** | | | | | | |
| **Difficult airway** | NR | 53/160 (33.1%) | 0.150 (0.034 to 0.653) | 0.011 | 0.206 (0.053 to 0.807) | 0.024 |
| **Cricothyroidotomy** | NR | 55/193 (28.5%) | 0.753 (0.200 to 2.839) | 0.675 | 0.974 (0.273 to 3.475) | 0.967 |
| **Vomiting or aspiration** | 12/53 (22.6%) | 61/197 (31.0%) | 0.653 (0.321 to 1.328) | 0.239 | 0.618 (0.313 to 1.220) | 0.165 |
| **Pneumothorax** | 5/18 (27.8%) | 60/209 (28.7%) | 0.955 (0.326 to 2.796) | 0.933 | 0.992 (0.344 to 2.858) | 0.988 |
| **Cardioversion** | 12/41 (29.3%) | 12/46 (26.1%) | 1.172 (0.457 to 3.005) | 0.740 | N/A | N/A |
| **Primary Organ Failure: Upper airway** | | | | | | |
| **Difficult airway** | 6/29 (20.7%) | 6/160 (3.8%) | 6.696 (1.990 to 22.531) | 0.002 | 3.401 (1.126 to 10.269) | 0.030 |
| **Cricothyroidotomy** | 5/13 (38.5%) | 16/193 (8.3%) | 6.914 (2.023 to 23.629) | 0.002 | 5.530 (1.627 to 18.804) | 0.006 |
| **Vomiting or aspiration** | NR | 20/197 (10.2%) | 0.722 (0.236 to 2.212) | 0.569 | 0.653 (0.216 to 1.971) | 0.449 |
| **Pneumothorax** | NR | 20/209 (9.6%) | 1.181 (0.253 to 5.513) | 0.832 | 1.133 (0.206 to 6.232) | 0.886 |

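### The autopsy criterion for upper airway oedema is limited by degree of swelling but not by prior instrumentation, so the upper-airway rows of Table S3 need a sensitivity analysis without autopsy-only evidence.

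*Combined protocol and SAP*

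**What the plan says.** In protocol Table 1 (Upper Airway Oedema present), oedema is coded as present if any one of five signs is recorded. Two of the five concern the larynx seen directly: "Obvious laryngeal swelling at 1^st^ laryngoscopy" and "Gross macroscopic laryngeal swelling at autopsy". The purpose box notes that swelling may follow multiple laryngoscopy attempts, states that "first laryngoscopy and autopsy findings have been qualified to take this confounding element into consideration", and adds: "Number of laryngoscopy attempts is recorded during data extraction". Table S1 gives the limit on the autopsy sign: "Recorded as Negative/No Upper airway involvement if only microscopic/minor laryngeal swelling at autopsy".

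Presence is not the analysed outcome. Under Data Variables, the signs are "to be identified in the immediate lead up to cardiorespiratory arrest in each case". Table 1 defines primary organ failure as the type that contributed most to the arrest, and it offers an unable-to-determine code. The same table bars coding a cardiovascular reaction after an arrest from isolated airway oedema or bronchospasm, unless vasopressor support is prolonged. There is no counterpart for airway swelling found after instrumentation.

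The SAP (Secondary Objectives) compares primary organ failure by complications, including FONA and "Difficult airway (FONA, failed intubation, or 3 or more attempts at intubation". Section 6.1 makes these analyses descriptive and unadjusted. For upper-airway failure and difficult airway, Table S3 gives a complete-case odds ratio of "6.696 (1.990 to 22.531".

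**The concern.** The two qualifications do different work. Restricting laryngoscopy to the first look removes swelling caused by later attempts. Restricting autopsy to gross swelling removes trivial findings, but it does not separate allergic swelling from swelling caused by instrumentation, which may also be gross. The number of attempts helps to define difficult airway, but it does not condition the coding of oedema.

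A sign that can support allocation to upper airway can therefore be produced by the repeated attempts that define the complication it is compared with. Some of the association could then run from the complication to the coded organ failure. At stake is whether Table S3 can be read as upper-airway anaphylaxis making airway management difficult. Those two rows have the largest odds ratios in that table.

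**Working it through.** **Inputs** (Table S3, upper airway, complete case)
- Difficult airway: 6/29 with the complication, 6/160 without.
- Cricothyroidotomy, taken here as the SAP's FONA: 5/13 with, 16/193 without.
- Number of these allocations resting on autopsy alone: not given. It is treated below as an assumption, k.

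**Formula.** With a and b the upper-airway and other deaths among those with the complication, and c and d the same among those without:
- OR = ad/(bc)
- SE of ln OR = sqrt(1/a + 1/b + 1/c + 1/d)
- 95% CI = exp(ln OR ± 1.96 × SE)

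This equals unadjusted logistic regression on one binary covariate.

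**Reproducing Table S3**
- Difficult airway: 6 × 154/(23 × 6) = 6.696; SE = sqrt(1/6 + 1/23 + 1/6 + 1/154) = 0.619; CI 1.990 to 22.531.
- Cricothyroidotomy: 5 × 177/(8 × 16) = 6.914; SE = sqrt(1/5 + 1/8 + 1/16 + 1/177) = 0.627; CI 2.023 to 23.629.

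Both agree with the table.

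**Scenario A: k exposed upper-airway cases move to another organ; the comparison group is unchanged**

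| Row | k | OR | 95% CI |
|---|---|---|---|
| Difficult airway | 1 | 5 × 154/(24 × 6) = 5.35 | 1.51 to 18.90 |
| Difficult airway | 2 | 4 × 154/(25 × 6) = 4.11 | 1.08 to 15.59 |
| Difficult airway | 3 | 3 × 154/(26 × 6) = 2.96 | 0.70 to 12.59 |
| Cricothyroidotomy | 1 | 4 × 177/(9 × 16) = 4.92 | 1.36 to 17.76 |
| Cricothyroidotomy | 2 | 3 × 177/(10 × 16) = 3.32 | 0.83 to 13.30 |

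Excluding the cases instead of reassigning them gives slightly higher values: 3.35 (0.78 to 14.32) for three difficult-airway cases, and 4.15 (1.00 to 17.20) for two cricothyroidotomy cases.

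**Scenario B: autopsy-only evidence is equally common in both groups.** Moving two of six difficult-airway cases and two of six comparison cases gives 4 × 156/(25 × 4) = 6.24 (1.47 to 26.6), close to the published value.

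The outcome therefore turns on whether autopsy-only evidence is concentrated in instrumented deaths. The documents do not say.

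**The two rows are not independent.** FONA is a component of difficult airway. If the composite was coded as defined, the five cricothyroidotomy cases lie within the six difficult-airway cases, so the second row adds little separate support.

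**The case against.** The case on the other side is substantial.

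- **The autopsy sign is qualified.** A reader might infer that the protocol promised a qualification and gave none. Table S1 and Table 1 both limit the sign to gross swelling. The gap is in the kind of qualification.
- **Presence is not primary failure.** A reader might infer that the complication creates the organ failure. Allocation requires a judgement about what drove the arrest. Two clinicians extract data independently, unresolved differences go to a panel, and there is a code for insufficient information. Table 1 even gives oedema seen at laryngoscopy in a bronchospasm death as an example of secondary failure. If the rule is followed, attempts made after the arrest should not make upper airway primary. This stands, and it narrows the route considerably. It does not close it: the autopsy sign is undated, no rule sends autopsy-only cases to the undetermined code, and no blinding of extractors to airway difficulty is described.
- **The forward direction is plausible and no causal claim is made.** The background says swelling makes intubation harder, and the SAP calls these analyses descriptive. Both are true, but a descriptive label does not help if the outcome is partly produced by its comparator.
- **FONA as a cause of swelling is an inference.** The documents name only multiple laryngoscopy attempts.
- **The scenarios are hypothetical, and the imputed odds ratios are lower**: 3.40 (1.13 to 10.27) and 5.53 (1.63 to 18.80). Imputation for missing data does not address how oedema was coded.
- **Reach into the primary result is not shown.** A reader might link the insect group's cricothyroidotomy frequency (5/28) to its upper-airway frequency (7/37). These have different denominators, and nothing shows that the same deaths are involved. The background already reports that respiratory involvement in venom deaths was predominantly upper airway. Recoding one insect case moves the unadjusted Insect v Drug odds ratio from 3.60 (1.17 to 11.07) to 6 × 108/(31 × 7) = 2.99 (0.93 to 9.54). However, the adjusted complete-case interval in Table S2c already includes 1 (0.927 to 13.468).

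**Conclusion.** The point holds in a limited form. The autopsy criterion is conditioned on degree and not on instrumentation, although the protocol itself names repeated laryngoscopy as a cause of swelling and the SAP defines difficult airway partly by repeated attempts. The pre-arrest rule for primary failure reduces the reverse route without removing it.

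The size of any bias cannot be found from the documents. Under Scenario A, the difficult-airway interval includes 1 once three of six cases are reassigned, and the cricothyroidotomy interval does so once two of five are. Under Scenario B the odds ratio barely moves. These figures show how few cases the associations rest on. They are not evidence that the associations are artefact, and the documents do not support saying so. Nor do they support calling the autopsy sign unqualified or saying that the primary allergen comparison is compromised. A low-cost sensitivity analysis is warranted because it can change what Table S3 supports.

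**What to change.** Keep the definition of upper airway oedema and add the following beside the current results.

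1. Use the free-text field on evidence of upper airway oedema to flag deaths allocated to upper airway on autopsy evidence alone.
2. Using the fields for number of intubation attempts, FONA and timing of intubation, report how many flagged deaths had more than one attempt or FONA, and whether intubation came before or after arrest. Counts below five would follow the ethics reporting limit. If none are flagged, a sentence saying so settles the matter.
3. Repeat the upper-airway rows of Table S3 and, secondarily, Table S2c, setting aside autopsy-only evidence in all deaths. Applying this to every death matters: discounting it only in instrumented deaths would make the outcome definition depend on the complication and lower the odds ratio mechanically. The instrumented-only version can be an optional second analysis, labelled with that limitation.
4. If the estimates fall materially, do not interpret the difficult-airway and cricothyroidotomy associations as upper-airway anaphylaxis leading to airway difficulty.

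The cost is re-reading the evidence text for a small set of deaths (5 + 16 = 21 upper-airway deaths appear in the cricothyroidotomy row) and refitting simple models. The downside is that some true upper-airway deaths known only from autopsy are lost in the sensitivity version, which is why both versions should be shown.
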